Ganeshkumar et al., 2024), such as language barriers, limited integration with regional healthcare systems, lack of user-centred design, and affordability concerns. Due to these gaps, many hypertensive patients struggle with self-monitoring and adherence to treatment regimens, leading to poor disease control and increased risk of complications. There is a pressing need for an affordable, user-friendly, and culturally appropriate mHealth application that caters to the Indian population.

To address these challenges, this study aims to develop and evaluate a customised mHealth application designed explicitly for hypertensive individuals in India. The proposed application will include Multi-language support, Blood pressure monitoring, Medication reminders, Physical activity tracking, Diet and lifestyle recommendations, Graphical progress reports, and Health alerts and emergency notifications.

While this study focuses on the Udupi district of Karnataka and incorporates Kannada language support, we recognise that India’s linguistic and cultural diversity presents unique challenges for nationwide mHealth implementation. Our choice of the Udupi district as the study site is strategic, as it represents a mixed urban-rural demographic typical of many Indian coastal regions, with established healthcare infrastructure and moderate smartphone penetration. The methodological framework and user-centred design principles employed in this study are designed to be adaptable across different linguistic and cultural contexts. However, direct generalizability will require validation studies in other Indian states’ languages and cultural nuances.

Given the growing burden of hypertension in India and the limitations of existing mHealth solutions, a customised, locally relevant, and patient-centric application can improve disease self-management, enhance patient engagement, and ultimately contribute to better hypertension control. This study will develop and test a novel mHealth intervention to assess its effectiveness in promoting self-monitoring, adherence, and improved health outcomes among hypertensive individuals in a community-based setting.

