**Figure 3. f3:**
[figure not shown]
The process of Android software development.

Figure 3 shows the process of android software development.

Finally, requirement analysis will be carried out by the investigator along with experts by obtaining the requirements from the end-users. Based on the requirement, an investigator will design the mHealth application which includes various modules, layouts, tabs, widgets, and contents. The coding of the application will be done by the software developer with the help of an investigator. The developed application will be tested for quality assurance and will be pilot tested among the participants. The investigator will be involved in the front and backend process of software development. The application development process will occur from January to July 2023, followed by the pilot study from August to September 2023. All feedback from the pilot study will be incorporated, and the final application version will be prepared by the end of September 2023. This ensures that Phase 3 (the randomised controlled trial) begins in October 2023 with a thoroughly tested and refined intervention.

The application will consist of blood pressure monitoring (Bluetooth enabled as well manually entered), weight, height, body mass index (BMI), medication reminder and physical activity (step count), and graphical reports of BP and weight. Weekly and monthly summaries (which can be converted into PDF and shared), abnormal warnings, Dietary Approaches to Stop Hypertension (DASH) diet plan, health education material, and recent updates on hypertension management will also be provided.

*Emergency alert protocol and safety measures*

Emergency alerts will be triggered when systolic BP exceeds 180 mmHg or diastolic BP exceeds 110 mmHg on two consecutive readings within 24 hours, or when systolic BP falls below 90 mmHg. The alert system operates on multiple levels: (1) immediate on-screen notification advising participants to seek medical attention; (2) automated SMS to the participant’s designated emergency contact (identified during enrollment); and (3) notification to the study team’s 24/7 monitoring system, enabling direct contact with participants and their healthcare providers. To address ethical concerns, all participants will provide informed consent for this monitoring protocol, designate emergency contacts, and receive clear instructions about when to seek immediate medical care independent of app alerts.

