*Recent updates on hypertension management*

The application will provide evidence-based health education content updated monthly, including: (1) medication adherence tips and side effect management; (2) lifestyle modification strategies (diet, exercise, stress management); (3) seasonal health considerations (e.g., BP management during extreme weather); and (4) simplified summaries of relevant clinical guidelines. Content will be reviewed by cardiologists and community medicine specialists before dissemination, with sources attributed and language appropriate for diverse educational backgrounds.

### Phase 3

After successfully completing the pilot study and incorporating user feedback, the refined mHealth application will be evaluated through a community-based cluster randomised controlled trial. The pilot study participants will not be included in this main trial to maintain methodological rigour and prevent contamination.

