It will be similar to that of the cluster-level analysis except for the fact that adjustments will be made for clustering. Hierarchical regression modelling will be employed to adjust for intracluster correlation in statistical comparisons due to participants being nested within village clusters, enabling assessment of the mHealth intervention’s impact on both individual and cluster-level outcomes while accounting for potential confounders, including age, gender, baseline blood pressure, and medication adherence. In addition, the values of the intra-cluster correlation coefficient for the various outcome measures will also be reported. Subgroup analyses will be carried out and a multiplicity of analyses will be addressed.

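### The hierarchical model adjusts for medication adherence, which the app is meant to change, without limiting that covariate to its baseline value

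*Protocol article*

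**What the plan says.** In Phase 3, under individual-level analysis, the protocol article sets out its adjusted model: "Hierarchical regression modelling will be employed to adjust for intracluster correlation in statistical comparisons due to participants being nested within village clusters". The model is to assess the app's impact while "accounting for potential confounders, including age, gender, baseline blood pressure, and medication adherence". In that list the word baseline stands directly before blood pressure. Nothing says when adherence is measured.

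Elsewhere the article treats adherence as something the app should change:

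- The Introduction says the study will "assess its effectiveness in promoting self-monitoring, adherence, and improved health outcomes among hypertensive individuals in a community-based setting".
- The description of the application in Phase 2 includes "medication reminder and physical activity (step count), and graphical reports of BP and weight".
- The section on recent updates on hypertension management promises monthly content that covers "medication adherence tips and side effect management".
- The sample size text in Phase 3 takes its assumed 5 mmHg from reviews of intervention packages in which medication reminders are one component.

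The baseline measurements listed in Phase 3 are blood pressure, knowledge and practice, self-efficacy and health status. Adherence itself is not named, although the list is worded as examples. The only adherence-related instrument named is MASES, which measures self-efficacy for adherence and is taken before and after the intervention.

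**The concern.** A confounder is a common cause of exposure and outcome. Adherence after randomisation cannot be a cause of a village's allocation. On the article's own rationale it is a consequence of allocation and a step on the path from app to blood pressure, which makes it a mediator.

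Putting a mediator in the effect model changes the question. The arm coefficient then describes the effect that does not pass through adherence, whereas the trial asks whether offering the app lowers blood pressure at all. A further problem arises if something unmeasured affects both adherence and blood pressure. Holding adherence fixed then links that factor to arm and breaks the balance that randomisation gave.

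As worded, the plan permits this. A reader of the results could not tell from the protocol whether the adjusted estimate was meant as the total effect.

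**Working it through.** **Plan's own figure.** The article gives no figure for how much of the effect runs through adherence, so there is nothing to reproduce on that point. The one plan figure needed is the assumed effect of 5 mmHg in systolic pressure (Phase 3, sample size). The sample size of 118 per arm plays no part in the argument.

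**Step 1: what the adjusted coefficient estimates.** Write the total reduction as Δ = direct part + part acting through adherence, and let s be the share acting through adherence. In a linear model without interaction and without an unmeasured common cause of adherence and blood pressure:

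- arm coefficient without adherence in the model: Δ
- arm coefficient with baseline adherence: Δ, because a value taken before the intervention cannot be changed by it
- arm coefficient with on-study adherence: Δ × (1 − s)

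**Step 2: numbers.** With Δ = 5 mmHg and s as an assumption shown over a range:

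- s = 25%: 5 × 0.75 = 3.75 mmHg
- s = 50%: 5 × 0.50 = 2.5 mmHg
- s = 75%: 5 × 0.25 = 1.25 mmHg

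**Step 3: check by simulation.** Taken from the article: 12 villages of 20 participants, six per arm, ICC 0.05, SD 15 mmHg, total effect 5 mmHg. Assumed: one SD of adherence is worth 4 mmHg, and on-study adherence depends on baseline adherence with coefficient 0.5. The app then raises adherence by 5s/4 SD. Each setting was run 300 times, and the arm coefficient was fitted by least squares (all villages are of equal size). Mean estimated reduction in mmHg:

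| Assumed share s | Formula, on-study adjustment | No adherence term | Baseline adherence | On-study adherence |
|---|---|---|---|---|
| 25% | 3.75 | 5.19 | 5.20 | 3.95 |
| 50% | 2.50 | 4.99 | 4.99 | 2.53 |
| 75% | 1.25 | 5.04 | 5.01 | 1.24 |

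The loss from on-study adjustment, within the same runs, is 5.19 − 3.95 = 1.24, 4.99 − 2.53 = 2.46 and 5.04 − 1.24 = 3.80. The formula Δ × s gives 1.25, 2.50 and 3.75. The simulation therefore confirms the algebra. It is not evidence about the true share.

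**Step 4: collider bias.** The simulation has no unmeasured common cause, so it shows the mediation loss only. If general health-consciousness raises adherence and lowers pressure by other routes, then at equal adherence the app arm contains less health-conscious people and the estimate shrinks further. If more severe disease raises both adherence and pressure, the distortion runs the other way. The direction cannot be settled from the documents.

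**The case against.** The strongest reply is that the covariate may well be meant as baseline adherence. Age and gender need no qualifier, the word baseline can be read as covering both items that follow it, and calling the list potential confounders suggests characteristics that precede the intervention. The Phase 3 analysis text says baseline data will be reported for every variable collected. MASES has a pre-intervention value, and no separate follow-up adherence measure is named. With only six villages per arm, chance imbalance in baseline adherence is plausible and adjusting for it is sound. All of this stands. It means that on-study adjustment is a possibility the text leaves open and not something the plan states.

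It can also be said that covariate timing belongs in the analysis plan, which is not shown. That stands only in part. The article does not leave the covariate open: it names adherence, gives it the role of confounder and puts it in the model for the app's impact, while describing adherence elsewhere as a target.

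Three stronger readings are tempting and should be resisted:

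- A reader might infer that part of the effect is adjusted away. That follows only if adherence is measured after randomisation, which the article does not say.
- A reader might infer that the trial's main result is compromised. The article does not designate the hierarchical model as primary, and it also plans cluster-level comparisons, including repeated measures ANOVA and chi-square tests, with no mention of this adjustment.
- A reader might turn the shrinkage into a loss of power. With 118 per arm, SD 15 and the stated design effect of 1.45, the normal approximation gives about 57% at 5 mmHg and 36%, 19% and 8% at 3.75, 2.5 and 1.25 mmHg. These figures use the unadjusted SD, whereas this model also adjusts for baseline pressure, so they do not describe its power. They also bring in the separate question of whether the sample size is adequate.

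**Conclusion.** The point holds in conditional form. The plan names a variable that the app is designed to change as a confounder in its adjusted effect model and does not restrict it to a pre-intervention value. If the value entered is measured after randomisation, the estimated effect falls in proportion to the share that acts through adherence: from 5 mmHg to about 3.75, 2.5 or 1.25 mmHg at assumed shares of 25%, 50% or 75%, with possible collider bias of unknown direction on top. If it is the baseline value, there is no such loss.

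These sizes rest on a linear model without interaction and on shares for which the documents offer no source. The damage would be confined to the adjusted hierarchical model. That is still the analysis described as allowing for clustering when the app's impact is assessed, so the ambiguity should be removed before data are analysed.

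**What to change.** In the individual-level analysis paragraph, state that all covariates in the effect model are values measured before the intervention starts: age, gender, baseline blood pressure and, if wanted, baseline adherence or baseline MASES. Add that follow-up adherence, including follow-up MASES, will not be a covariate in any model used to estimate effectiveness. It should be analysed as an outcome, which also serves the aim given in the Introduction, or in a separately labelled mediation analysis with its assumptions stated.

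The cost is a sentence or two. No new data are needed if baseline MASES is used, because it is already planned. If adherence itself is wanted as a covariate, the article should name the instrument and include it among the baseline measurements.

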Whelton et al., 2018). The orientation protocol will include: (1) timing specifications requiring BP measurement twice daily (morning: 6-10 AM, evening: 6-10 PM) with at least 12 hours between readings; (2) standardised measurement technique involving three consecutive readings taken 1-2 minutes apart, with the first reading discarded and the mean of the second and third readings recorded; (3) pre-measurement requirements including 5 minutes of quiet rest, avoiding caffeine/exercise 30 minutes prior, proper cuff placement directly on skin (not over clothing), and maintaining feet flat on floor with back supported; (4) technical specifications ensuring appropriate cuff size selection and proper arm positioning at heart level; and (5) data entry protocols for recording measurements in the mHealth application immediately after each session. Participants will demonstrate competency in the BP measurement technique before the study commences, with refresher training provided at monthly follow-up contacts. The control group will receive standard care which includes advice to adhere to their prescribed medication and lead an active lifestyle. Baseline measurements like blood pressure, knowledge and practice of management of blood pressure, self-efficacy, and health status will be obtained from the recruited participants in both groups. Blood pressure will be measured with an electronic BP apparatus ([name] BP monitor-118), which will be calibrated periodically. Knowledge and practice will be assessed using a hypertension fact questionnaire. Self-efficacy using Medication Adherence Self-Efficacy Scale (MASES) and Self-Efficacy for Managing Chronic Disease 6-item Scale will be assessed and health status using SF-36 questionnaire will be assessed for pre and post-test (
Fernandez et al., 2008;
Lorig et al., 2001;
Ware & Gandek, 1998). For any reason, if the participant is unable to use the application, we will be discontinuing the intervention regimen for that participant. Regular phone calls will be made to remind them to use the application and to track their BP. The participants will be allowed to withdraw from the study at any given time as per their decision. The consort flowchart of the phase 3 is shown in
Figure 4.

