**Figure 4. f4:**
[figure not shown]
Phase 3 CONSORT flow diagram.

Data will be entered and analyzed using SPSS version 22. The outcomes will be analyzed at the cluster and the individual level by intention-to-treat as well as per protocol analyses. Baseline data of all collected variables will be reported at both the individual as well as at the cluster level. The flow of participants and clusters through the various stages of the trial will be depicted through a flow diagram, giving the absolute number and reasons for non-inclusion, and non-adherence at various steps from the point of approach, recruitment, randomization, a follow-up to analysis, in both the arms. The effectiveness will be analyzed according to the principles of both intention-to-treat as well as per-protocol analysis. Multiple Imputation techniques will be employed to address missing data, with sensitivity analyses conducted to determine the impact of missing data on results and the Last Observation Carried Forward method applied for cases with intermittent missing data in follow-up measurements.

*Cluster-level analysis*

Categorical data will be summarized as proportions and quantitative data as means (or medians) and standard deviations (or interquartile range). Risk will be estimated as Relative Risk (RR). Chi-square test, repeated measures ANOVA (or Friedman’s Test) will be used to compare the 2 groups and assess the significance of any difference therein. An estimate of the effect size for the various variables will be reported along with its precision as a 2-sided 95% confidence interval. A p-value of less than 0.05 will be taken as statistically significant. Regression models will be used according to standard protocols to find out significant factors affecting the intervention at the cluster level.

*Individual-level analysis*

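### The hierarchical model names baseline blood pressure as its only outcome baseline; the knowledge, self-efficacy and SF-36 comparisons should each be adjusted for their own baseline score

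*Protocol article*

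**What the plan says.** Under Individual-level analysis, the protocol article proposes hierarchical regression to handle the nesting of participants in villages. The model is described as "enabling assessment of the mHealth intervention’s impact on both individual and cluster-level outcomes". Its covariates are then introduced in these words: "accounting for potential confounders, including age, gender, baseline blood pressure, and medication adherence". No separate covariate list is given for any outcome.

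The Phase 3 text on intervention and measurements, just before the CONSORT diagram, says: "Baseline measurements like blood pressure, knowledge and practice of management of blood pressure, self-efficacy, and health status will be obtained", in both groups. It names the instruments (a hypertension fact questionnaire, MASES, the 6-item chronic disease self-efficacy scale, SF-36) and their timing; for example, "health status using SF-36 questionnaire will be assessed for pre and post-test".

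Under Cluster-level analysis: "Chi-square test, repeated measures ANOVA (or Friedman’s Test) will be used to compare the 2 groups". The individual-level analysis is tied to this: "It will be similar to that of the cluster-level analysis except for the fact that adjustments will be made for clustering".

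The sample size paragraph identifies systolic BP reduction as the primary outcome.

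**The concern.** For a continuous outcome measured before and after, the baseline score on the same instrument is usually the strongest predictor of the follow-up score. The printed list gives systolic BP its own baseline. For the questionnaires it names a baseline (BP) that is likely to be only weakly related to the score, and it does not name the one that matters. An analyst who followed the named covariates would adjust SF-36 for blood pressure and not for baseline SF-36.

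Two things are at stake for these outcomes. The first is precision, since data already collected would not be put to best use. The second is chance imbalance: with six villages per arm, baseline differences in knowledge or self-efficacy can easily arise, and adjusting for BP does little to correct them. The article's Results and Conclusion statements rest the application's promise on health status, knowledge and self-care, which are largely the outcomes concerned. The trial is also open-label, so a covariate choice left open may be settled after data have been seen.

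**Working it through.** **Inputs from the article.** 118 participants per arm; six villages per arm; ICC 0.05; stated design effect 1.45; clusters of about 20; 15% attrition.

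**Assumptions, not in the article.** Pre/post correlation r of a score between 0.4 and 0.7, the same at village and individual level; ICC 0.05, given for the BP sample size, also applies to the scores; BP is nearly unrelated to the scores (a correlation of 0.1 would leave 1 − 0.01 = 0.99 of the variance), so a BP-only model behaves like a post-only one.

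**The plan's own figure.** The article gives no precision or power for the questionnaires. Its one sample size is 118 per arm for systolic BP. The stated inputs (5 mmHg, SD 15, 90% power, two-sided 5%) give 190 per arm, 190 × 1.45 = 276, and 276/0.85 = 325, so 118 does not reproduce. That is a separate matter; 118 is taken here as the planned size.

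**Step 1: residual variance under each route**, relative to a post-only comparison (= 1). Adjusting for own baseline gives 1 − r². With one pre and one post measurement, the group-by-time test in repeated measures ANOVA is a comparison of changes, with factor 2(1 − r). The sample-size value of own-baseline adjustment is then 1/(1 − r²) against post-only and 2(1 − r)/(1 − r²) = 2/(1 + r) against change.

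| r | 1 − r² | 2(1 − r) | 1/(1 − r²) | 2/(1 + r) |
|---|---|---|---|---|
| 0.4 | 0.84 | 1.20 | 1.19 | 1.43 |
| 0.5 | 0.75 | 1.00 | 1.33 | 1.33 |
| 0.6 | 0.64 | 0.80 | 1.56 | 1.25 |
| 0.7 | 0.51 | 0.60 | 1.96 | 1.18 |

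Own-baseline adjustment has the smallest variance in every row. Below r = 0.5 the change contrast is worse than ignoring the baseline.

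**Step 2: power, for illustration.** Take an assumed effect of 0.4 SD with 118 × 0.85 = 100.3 analysed per arm.

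| Design effect | r | Post-only | Change | Own baseline |
|---|---|---|---|---|
| 1.45 | 0.5 | 65% | 65% | 78% |
| 1.45 | 0.7 | 65% | 86% | 91% |
| 1.95 | 0.5 | 53% | 53% | 65% |
| 1.95 | 0.7 | 53% | 74.5% | 81% |

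The design effect of 1.95 is 1 + 19 × 0.05, for clusters of 20. These powers make no small-sample correction for having only 12 villages, so the differences matter more than the levels.

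**Step 3: chance baseline gap.** The SE of the standardised baseline difference is √(2 × DE/118).
- DE 1.45: √(2.9/118) = 0.157; P(|gap| > 0.2 SD) = 2(1 − Φ(0.2/0.157)) ≈ 0.20.
- 118/6 = 19.67 per village: DE = 1 + 18.67 × 0.05 = 1.93; SE = 0.181; P ≈ 0.27.

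Given a gap g, a post-only contrast shifts by r·g on average. For g = 0.2 and r = 0.6 that is 0.12 SD. The change contrast shifts the other way by (1 − r)·g = 0.08 SD. Own-baseline adjustment removes the expected shift.

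**The case against.** The strongest reply is that the covariates are introduced as examples, so nothing makes these four the complete set, or the same set for every outcome. A reader might infer that the baseline questionnaire scores are left out of the analysis. The text does not support that. Nor does it say outright that one fixed list serves all the questionnaires: the model sentence speaks of individual and cluster-level outcomes without naming instruments, and the broader phrase in "the values of the intra-cluster correlation coefficient for the various outcome measures will also be reported" concerns only ICC reporting.

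The plan also gives the pre-test scores a possible way in. Repeated measures ANOVA is named, the individual-level analysis is said to be similar, and the questionnaires are taken before and after. A group-by-time contrast uses the baseline as a response. Quoting 96% as the general cost would therefore be wrong; that figure holds only against a post-only model and only at r = 0.7.

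Finally, a covariate set per outcome is commonly left to the SAP, and naming baseline BP suits the primary outcome.

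Most of this stands, and it limits the point to what is written. Three things remain. The only outcome baseline that the article names fits only blood pressure. A change contrast uses the baseline less efficiently than adjustment does, at every r below 1. And the point does not ask for a missing list; it asks that one phrase in the printed list be worded so that it fits all the outcomes.

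**Conclusion.** The point holds as an improvement to the wording, not as proof of an omission. Neither named route adjusts each questionnaire score for its own baseline, and doing so is better than both. For r between 0.4 and 0.7 the gain is equivalent to 19% to 96% more participants against a post-only model, or 18% to 43% against a change contrast. It also corrects for a chance baseline gap, which exceeds 0.2 SD with probability of about 0.20 (design effect 1.45) to 0.27 (about 20 per village).

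These sizes rest on the assumed r and on carrying the BP ICC over to the scores; the article gives neither for the questionnaires. A reader might also infer systematic bias. Randomisation rules that out as a consequence of this choice alone: the harm is lost precision and uncorrected chance imbalance. Only non-primary outcomes are touched, because the systolic BP comparison already has its baseline named.

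**What to change.** In Individual-level analysis, replace *baseline blood pressure* in the covariate list with *the baseline value of the outcome being analysed*. This means baseline systolic BP for systolic BP, and the baseline hypertension fact questionnaire, MASES, 6-item self-efficacy or SF-36 score for each of those outcomes. Leave age, gender and medication adherence as they are; nothing here argues for dropping them.

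The cost is one phrase in the text and one covariate swapped in each questionnaire model. No new data are needed, and the sample size and the primary analysis are unchanged. If the SAP already specifies own-baseline adjustment, the edit only brings the article into line.
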